## Abstract

**Background/Objectives:** Fear of falling (FOF) and falls are prevalent issues among older adults, leading to activity restriction, decreased quality of life, and increased dependency. This study aims to assess the effectiveness of a nurse-led health education intervention to reduce FOF and fall incidence in older adults within primary care settings. **Methods:** This two-arm, multicenter, parallel, cluster-randomized clinical trial includes ten primary care centers in Spain and will enroll 150 adults over 65 years with FOF, mild or no functional dependence, and independent ambulation. Participants will be randomized to either the intervention group, which will receive five initial group education sessions led by community nurses and a booster session at six months, or the control group, which will receive usual care. Primary outcomes include FOF, assessed using the Short Falls Efficacy Scale-International (FES-I), and fall incidence. Data collection will occur at baseline, one month, six months, and twelve months post intervention. This study has been approved by the Ethics Committee for Research with Medicinal Products at Gregorio Marañón University Hospital in accordance with the Declaration of Helsinki. **Expected Outcomes:** The health education intervention is expected to significantly reduce both FOF and fall incidence, supporting the integration of FOF management in routine primary care for older adults, with potential benefits for safety and quality of life. Trial Registration: ClinicalTrials.gov: NCT05889910. The study protocol follows CONSORT and SPIRIT guidelines.

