### 2.2. Research Hypothesis

Implementation of a standardized nursing care plan for at least six weeks reduces FOF (defined as patients’ confidence in being able to perform activities of daily living without losing balance or falling, as measured by the short FES-I scale) by at least 3.8 points among independent community-dwelling individuals over 65 years of age at six and 12 months post intervention compared to usual clinical nursing practice in these patients.

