### 2.7. Sample Size

We expect to be able to recruit ten PCFs (five assigned to the intervention group and five to the control group). Assuming a significance level of 0.05, a difference of 3.8 points on the Short Falls Efficacy Scale-International (FES-I), a standard deviation of 5.1 points, and an intraclass correlation coefficient of 0.1, at least 12 participants will be required per center (a total of 120 participants) to reach a power of 80%. Allowing for a loss of 20%, the necessary sample size will be 150 individuals (75 patients assigned to the intervention group and 75 to the control group; approximately 15 patients in each PCF, about five patients per nurse).

Patients seen by nurses at each participating facility and meeting the eligibility criteria will be recruited using a consecutive sampling method until the required sample size—which will be the same for all participating facilities—has been reached.

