### 4.4. Data Analysis

A descriptive analysis by groups (intervention and control) of participants’ sociodemographic, functional, and clinical characteristics will be carried out to identify potential differences between the two study groups, with quantitative variables expressed as either means and standard deviations or medians and interquartile ranges depending on the normality or skewness of data distribution. Qualitative variables will be summarized as frequencies and percentages. Data on the effect of the health education intervention will be analyzed in both the intention-to-treat population and the per-protocol population. In the former case, all participants will be included and will be analyzed as part of the group to which their PCF will be randomly assigned. Should the percentage of missing data be higher than 5%, multiple imputation techniques will be used. In the per-protocol analysis, complete cases of patients will be included provided they have maintained adherence. The intervention group is required to be adherent and have at least 80% attendance at the initial five sessions. Safety, acceptability, and feasibility of the health education intervention will also be assessed.

The primary efficacy analysis, (FOF), will be the comparison between intervention and control groups fitting a fixed-effects ANOVA model. Model will include group and facility as independent variables, with facility being a nested factor within group. The short FES-I scale mean scores and their 95% confidence intervals will be provided for each facility, or by groups if no differences between facilities are observed. The effectiveness of the health education intervention in relation to fear of falling will be measured through the decrease in the short FES-I scale scores, assessed at three times: at 1-, 6- and 12 months after the intervention. The difference in means between the intervention and control groups will be analyzed. In addition, the variable will be examined dichotomously, using a cut-off point on the short FES-I scale of 11 or more to identify the presence of fear of falling. Multivariate models will be fitted to identify factors potentially related to FOF.

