For the secondary outcome variable (incidence of falls), a process similar to the main analysis will be followed, but this time fitting a fixed-effects logistic regression model, again nesting each facility within its group. The effectiveness of the health education intervention for the incidence of falls will be measured through the recording of falls (recorded in the medical history or reported by the patient), at 1-, 6- and 12-months post intervention. Both groups will be compared in terms of odds ratios, and their corresponding 95% confidence intervals will be provided.

To assess the impact of the health education intervention by time, mixed effects models will be adjusted, including time also as an independent variable and random intercepts for participants.

Data will be recorded in a paper data collection notebook and entered into an Excel spreadsheet by a single researcher in order to minimize the risk of transcription errors. The collected data will then undergo a second review to correct transcription errors, if necessary. Access to these data will be limited to authors until open access dissemination, after which they can be included on ClinicalTrials.gov.

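### The primary endpoint is stated inconsistently: the deciding visit differs between the hypothesis, the analysis and the sample size, and the abstract promotes falls to primary

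*Protocol article*

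**What the plan says.** All references are to the protocol article.

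- **2.2 Research Hypothesis** sets a reduction of at least 3.8 points on the short FES-I "at six and 12 months post intervention compared to usual clinical nursing practice".
- **4.4 Data Analysis** makes fear of falling the primary efficacy analysis. It fits a fixed-effects ANOVA with group and facility nested in group, and says the effect is "assessed at three times: at 1-, 6- and 12 months after the intervention". The model has no time term, and no visit is singled out. Separate mixed models that include time are described later in 4.4 but are not called primary.
- **2.11.1** names the short FES-I as the primary outcome and lists every visit at which it is collected, without marking one as primary.
- **2.7 Sample Size** opens its calculation with "Assuming a significance level of 0.05, a difference of 3.8 points". It describes one comparison and does not say at which visit.
- **The abstract** says "Primary outcomes include FOF, assessed using the Short Falls Efficacy Scale-International (FES-I), and fall incidence".
- **The body** treats falls as secondary in the objectives (2.1.2), the outcome list (2.11.2), Table 2 and 4.4, where the falls paragraph begins "For the secondary outcome variable (incidence of falls".

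**The concern.** A confirmatory trial needs one rule that says which result, at which time, counts as success. Here the hypothesis points to two visits and the primary analysis to three, while the sample size points to one unnamed comparison. The abstract adds a second outcome.

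The visits are not interchangeable. Under 4.3 the six-month assessment always precedes the booster session, and in the intervention arm the 12-month assessment falls six months after it. A six-month result therefore tests the initial course, and a 12-month result tests the course plus the booster.

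The trial is open (2.3), and 2.9 says that the principal investigator assesses the results unblinded. If the deciding visit is left open, it can be settled after the data are seen, and the result could be presented on the most favourable visit. The choice also determines whether the calculation in 2.7 matches the primary test.

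**Working it through.** **Inputs.** From 2.7: "Assuming a significance level of 0.05" (sidedness not stated; two-sided assumed), "a difference of 3.8 points on the Short Falls Efficacy Scale-International (FES-I", "a standard deviation of 5.1 points", intraclass correlation 0.1, five facilities per arm, 12 evaluable per facility, 80% power and 20% loss. The document gives no correlation between the test statistics at different visits, so I assume 0.5 to 0.9 and show the range.

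**Step 1: reproduce the plan's sample size.**
- Per arm without clustering: n = 2 × [5.1 × (1.960 + 0.842) / 3.8]² = 28.3.
- Per facility with k = 5 per arm: m = n(1 − ICC) / (k − n × ICC) = 28.3 × 0.9 / (5 − 2.83) = 11.7, so 12 per facility and 120 in total.
- Design effect at 12 per facility: 1 + 11 × 0.1 = 2.1. Effective n per arm: 60 / 2.1 = 28.6. Normal-approximation power: 80.4%.
- Recruitment: 120 / 0.8 = 150.

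The stated 120 and 150 reproduce, and they fit one comparison at 0.05. I keep the normal approximation below because it returns the plan's figures; whether it suits ten clusters is a separate question.

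**Step 2: false-positive chance if any one visit could be claimed at 0.05.** With independent tests it is 1 − 0.95² = 9.8% for two and 1 − 0.95³ = 14.3% for three. Repeated scores on the same people are correlated, which lowers this. Simulation of equicorrelated normal statistics (2 million draws) gives:

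| Assumed correlation | 6 and 12 months | 1, 6 and 12 months |
|---|---|---|
| 0.5 | 9.1% | 12.5% |
| 0.7 | 8.3% | 10.9% |
| 0.9 | 7.0% | 8.4% |

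**Step 3: false-positive chance if both 6 and 12 months must succeed.** A false claim requires a false positive at a visit with no effect, so the rate cannot exceed 5%. With no effect at either visit it is 0.9% to 3.0% at correlations of 0.5 to 0.9.

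**Step 4: power under each rule, at 12 per facility.** This assumes the same 3.8-point effect and SD at each visit.
- One named visit at 0.05: 80.4%; 120/150 unchanged.
- Both visits required: at most 80.4%, and at least 2 × 80.4% − 100% = 60.8%. The position in that interval depends on the correlation.
- Any visit, with a Bonferroni split: for two visits, each test at 0.025 has 71.7% power, and about 20 per facility would be needed for 80%. For three visits, each test at 0.0167 has 66.4% power, and about 28 per facility would be needed. These are powers at a single visit.

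The sample size in 2.7 therefore carries over unchanged only to the first rule.

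**The case against.** The best defence is that nothing in the document commits the sponsor to an inflated error rate. The 0.05 level appears only in 2.7. Section 4.4 promises mean differences, odds ratios and 95% confidence intervals, with no significance level per visit and no statement that one visit suffices. A multiplicity procedure is commonly left to a statistical analysis plan, which may exist. The hypothesis in 2.2 reads naturally as requiring both visits, and on that reading the false-positive rate is not inflated. All of this stands. A reader might infer that the protocol tests each visit at 0.05 without adjustment, so that inflation is an established fact. The text does not support that; the inflation is conditional on an any-visit rule.

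A reader might also count six primary tests, three for FES-I and three for falls. That gives one sentence of the abstract more weight than a consistent body: 2.1.1 has fear of falling as the only primary objective, falls are secondary everywhere outside the abstract, and 2.7 sizes the trial on FES-I alone.

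On the correlations, 2.11.1 reports one-month test-retest values for the scale (intraclass correlation 0.77, Spearman 0.99). These favour the upper part of my range at short intervals, and hence the smaller inflation figures. Longer intervals may correlate less.

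The defence does not remove the conflict itself. Sections 2.2 and 4.4 name different sets of visits for the same primary question, and a later analysis plan that chose either set would still contradict the other section. The mixed models in 4.4 do not settle it, because they are not designated primary.

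**Conclusion.** The concern holds as an inconsistency in the protocol's own statements, one that a later analysis plan cannot remove without contradicting one of them. The primary visits conflict between 2.2 and 4.4, 2.7 is tied to no visit, and the abstract contradicts the body on falls.

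The statistical consequence depends on the rule intended. Under an any-visit rule at 0.05, the false-positive chance is about 8-12.5% for three visits and 7-9% for two. Under a both-visits rule it is at most 5%, with joint power no higher than the single-test 80.4%. These figures assume two-sided tests with valid standard errors and between-visit correlations of 0.5-0.9, which the document does not supply. The wording conflict needs no assumption. The point should be corrected, and the correction is one of wording unless the sponsor chooses a rule that lowers power.

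**What to change.** State one decision rule, in the same terms, in 2.2, 2.7, 2.11.1 and 4.4. The choice is the sponsor's:

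- **One primary visit.** Twelve months is one candidate, since sections 5 and 6 stress the longer follow-up, although section 5 also values the short-term result. Six months could then be tested at 0.05 only if the primary visit is significant. This holds the error rate at 5% for the two visits and leaves 120/150 unchanged. If 12 months is chosen, the text should address that 4.3 times this visit from randomization in controls and from the booster in the intervention arm.
- **Both 6 and 12 months required.** Say so explicitly, test each at 0.05, and restate the power in 2.7 for joint success. This stays closest to 2.2, but power may fall below 80% at the present size.

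Under either rule, make the 1-month comparison secondary, say in 2.7 which comparison the calculation serves, and correct the abstract so that falls are secondary.

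The cost is a few sentences, plus a revised power statement under the second option. The trade-off is that an effect seen only at a non-primary visit could no longer be claimed as the primary result.

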### 2.8. Randomization

Ten PCFs will be randomly assigned to the intervention or control group, resulting in five facilities per arm. An allocation ratio of 1:1 will be used. The randomization will be performed using a random number generator. The study coordinator will run the generator and place the allocations into sealed envelopes.

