#### 2.11.3. Explanatory Variables

Sociodemographic variables: sex, age, marital status, number of cohabiting individuals, level of education, personal net monthly income, current or previous occupation, availability and type of support at home, perceived ability to receive family support, neighborhood, basic healthcare district, the Medea index (used to measure social inequalities in Spain), time spent in the neighborhood in years, housing characteristics, most frequent type of housing in the neighborhood, accessibility to basic services, perceived safety and walkability of the neighborhood.Functional variables: the Downton scale, the Barthel index, the SPPB scale total score, four-meter gait disturbance, balance disturbance, loss of lower limb strength, the Lawton-Brody index, physical activity recommended for this age group by the Spanish Ministry of Health (i.e., 150 min of moderate physical activity or 75 min of vigorous physical activity; balance exercises; muscle strengthening exercises; flexibility exercises). Data on this variable will be collected separately, and patients will be considered as meeting the recommended physical activity level, provided that 75% of the activities are carried out. This will include a variable regarding how many dimensions (from one to four) are met by the patient.Clinical variables: falls in the previous year (pre intervention); falls during intervention; fall-associated injuries (pre intervention, during intervention, and post intervention); mild visual problems or use of glasses; mild hypoacusis, either unilateral or corrected with a hearing aid; use of a walking device; pain (using a verbal numerical scale); anxiety (via the Generalized Anxiety Disorder-7 (GAD-7) questionnaire); depression (via the Patient Health Questionnaire-8 (PHQ-8); ability to practice self-care (via the Appraisal of Self-Care Agency Scale-Revised (ASA-R)); cognitive level (using the Mini-Mental State Examination); perceived health status; body mass index; urinary incontinence, comorbidities (using the Charlson index); medication; polypharmacy; high blood pressure; nursing diagnosis of risk of falling.Usual footwear variables: heel height in centimeters, type of sole, sole material, type of fastening.Feasibility and acceptability variables:○Feasibility (to be measured among professionals): recruitment rate, randomization, adherence to the health education intervention, follow-ups performed, safety/adverse events, difficulties in implementing the health education intervention. To be assessed at the end of the clinical trial.○Acceptability (to be assessed in patients assigned to the intervention group):-Participants: at the end of the health education intervention, data on its utility, usability, satisfactoriness, recommendability, as well as other open questions will be collected.-Professionals: data on the utility, usability, and satisfactoriness of the program, as well as their readiness to repeat it and other open questions will be collected.

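### The falls model omits falls in the previous year, which forgoes a little power and leaves any chance imbalance in prior fallers in the odds ratio (minor)

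*Protocol article*

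**What the plan says.** Section 4.4 (Data Analysis) gives the terms of the main model: "Model will include group and facility as independent variables, with facility being a nested factor within group". For falls, "a process similar to the main analysis will be followed, but this time fitting a fixed-effects logistic regression model, again nesting each facility". On the effect measure, the section states: "Both groups will be compared in terms of odds ratios, and their corresponding 95% confidence intervals will be provided". For the effect over time, "mixed effects models will be adjusted, including time also as an independent variable and random intercepts for participants". Multivariable work is named for fear of falling only: "Multivariate models will be fitted to identify factors potentially related to FOF". Section 4.4 names no baseline covariate for the falls comparison.

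Section 2.11.3 lists, among the explanatory variables, "Clinical variables: falls in the previous year (pre intervention); falls during intervention". Table 2 places the clinical variables at the pre-intervention baseline visit.

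On allocation, section 2.8 says: "Ten PCFs will be randomly assigned to the intervention or control group, resulting in five facilities per arm". It describes a random number generator and mentions no stratification or matching. The safeguards listed in section 4.5 concern group size, attrition, eligibility criteria and training, and none balances fall history.

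**The concern.** Whether a participant fell in the year before the trial is the pre-trial value of the falls outcome. It is already collected, yet the stated treatment comparison does not use it.

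With only five facilities per arm, the share of prior fallers can differ between arms by chance. The facility terms do not remove such a gap. In the nested model the arm contrast is the average of the facility log odds in one arm minus the average in the other, so facilities with more prior fallers raise their own arm's average.

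If the baseline table shows a gap and nothing has been fixed beforehand, the team must either leave the estimate shifted or decide to adjust after seeing the data.

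**Working it through.** **The plan's own figure.** The stated sample size concerns the short FES-I. Per arm without clustering, n = 2 × (1.960 + 0.842)² × 5.1² / 3.8² = 28.3. With five facilities per arm and ICC 0.1, the number per facility is 28.3 × 0.9 / (5 − 2.83) = 11.7, so 12. That gives 120 evaluable and 120 / 0.8 = 150 recruited, as stated. No power is stated for falls.

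**Inputs for falls.** From the introduction: an annual incidence of 30 to 40% (midpoint 35% used for controls) and about 30% prior fallers. Assumed: up to 50% prior fallers, since everyone enrolled has fear of falling; a prior-fall odds ratio of 2, 3 or 5; a treatment odds ratio of 0.5; facility ICC of prior falls from 0 to 0.1.

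**Step 1: how likely is a gap?** The SD of the arm difference in the share p of prior fallers is √[2p(1−p)/75 × (1 + 14 × ICC)].
- p = 0.3, ICC 0: √0.0056 = 0.075. The chance of a gap above 10 points is 18%.
- p = 0.5, ICC 0: 0.082, chance 22%.
- p = 0.3, ICC 0.1: √(0.0056 × 2.4) = 0.116, chance 39%.
- p = 0.5, ICC 0.1: 0.126, chance 43%.

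**Step 2: what does a 10-point gap do with no treatment effect?** Take a prior-fall odds ratio of 3, 30% prior fallers and 35% overall risk. The risks are then about 0.273 without and 0.530 with a prior fall.
- Arm with 35% prior fallers: 0.65 × 0.273 + 0.35 × 0.530 = 0.363.
- Arm with 25%: 0.75 × 0.273 + 0.25 × 0.530 = 0.337.
- Odds ratio: (0.363/0.637) / (0.337/0.663) = 1.12.

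Across prior-fall odds ratios of 2, 3 and 5 and shares of 30 and 50%, a 10-point gap gives 1.07, 1.11–1.12 and 1.16–1.18. A 20-point gap gives about 1.15, 1.24–1.25 and 1.35–1.39.

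**Step 3: standard error and power.** Asymptotic logistic information, 60 evaluable per arm, 30% prior fallers, no facility terms. Relative efficiency is (z adjusted / z unadjusted)², with z = log OR / SE. The last column is a simulation of the facility-within-arm logistic model: 10 facilities of 12, 50% prior fallers, ICC 0.05, 4,000 runs per setting.

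| Prior-fall OR | SE, unadjusted to adjusted | Log OR, unadjusted to adjusted | Relative efficiency | Simulated power |
|---|---|---|---|---|
| 2 | 0.415 to 0.420 | −0.678 to −0.693 | 1.021 | 31.0% to 31.3% |
| 3 | 0.413 to 0.426 | −0.654 to −0.693 | 1.055 | 28.6% to 29.8% |
| 5 | 0.410 to 0.440 | −0.609 to −0.693 | 1.127 | 26.1% to 28.9% |

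The standard error rises. The log odds ratio moves away from zero by proportionally more, so the test gains slightly. In null simulations the correlation between estimate and imbalance fell from 0.19–0.42 to about zero with adjustment. Null rejection was 5.1–5.9% unadjusted and 4.8–5.5% adjusted.

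**Limit of the simulation.** Runs without a finite estimate, mainly because a facility had no falls, were dropped: about 6–7% under the null and 26% at a treatment odds ratio of 0.5. That is a separate difficulty of facility fixed effects, which this covariate does not cure.

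**The case against.** *The omission is not an error of validity.* This stands. Chance imbalance under randomization is random error, not systematic bias. A shift to 1.07–1.18 is 0.07–0.17 on the log scale, or roughly 0.2–0.4 of a standard error of 0.41. A reader might infer that the falls test is biased or rejects too often because of this omission; the null rejection rates above do not show that.

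*Adjustment does not improve precision.* This also stands. A reader might carry over the linear-model argument and say that the odds ratio loses precision without the covariate. For a logistic odds ratio the adjusted standard error is the larger one, and the gain lies in power.

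*The strength of prior falls as a predictor is assumed.* True. The introduction names prior falls as a risk factor for fear of falling but does not list them among the risk factors for falls. Its figures do point to clustering within people. If 30% fall at least once and falls are Poisson, λ = −ln 0.7 = 0.357, and 1 − 0.7 − 0.7 × 0.357 gives 5% repeat fallers. If the 30% means exactly one fall (45% fallers in all), λ = −ln 0.55 = 0.598, and 1 − 0.55 − 0.55 × 0.598 gives 12%. The text gives more than 15%. This supports the direction but does not fix the size.

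*Covariates may be left to an analysis plan not shown.* This carries partial weight. The article does state the model terms, and the falls analysis copies them. A secondary objective relates clinical variables to falls, so prior falls are not ignored altogether; but that is a risk-factor analysis and does not adjust the treatment odds ratio.

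**Conclusion.** The point holds, at minor severity. The stated falls comparison leaves out a baseline value of its own outcome that is already collected. The cost is about 0.3 to 2.8 percentage points of power, plus an uncorrected shift in the odds ratio if prior fallers happen to be unevenly spread. Both figures rest on assumed prior-fall odds ratios of 2 to 5 and a 35% control risk; the power figures also assume a treatment odds ratio of 0.5.

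The abstract lists fall incidence among the primary outcomes, which might tempt a reader to rate this higher. Sections 2.1.2, 2.11.2 and 4.4 and Table 2 all treat falls as secondary, and the sample size is set for the short FES-I alone.

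**What to change.** In section 4.4, pre-specify falls in the previous year (yes/no) as a participant-level covariate in the falls comparison and in the by-time falls model, whether or not the arms look balanced. Report the unadjusted odds ratio as a sensitivity analysis.

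This takes about a line of text and no new data. It has two costs:
- The odds ratio becomes conditional on prior falls, and the report should say so.
- At one month events may be too few for the adjusted model to be estimated reliably. With a constant hazard and 30–40% annual incidence, the one-month risk is 1 − 0.7^(1/12) = 2.9% to 1 − 0.6^(1/12) = 4.2%, or about 4 to 6 fallers among 120 to 150 people. With five fallers spread at random, about 10 × 0.9⁵ = 5.9 of the ten facilities would have none. The main benefit is therefore at 6 and 12 months.
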